## Abstract

**Background:**

Structured exercise training has been proposed as a useful adjunctive therapy for Crohn’s disease by improving immune function and psychological health, reducing fatigue and promoting gains in muscle and bone strength. However, the evidence for exercise in Crohn’s disease is sparse, with only a handful of small prospective trials [1, 2], with methodological limitations, including the use of non-randomised and non-controlled study designs and small sample sizes. Here, we describe the protocol for a study that aims to assess the feasibility and acceptability of two common types of exercise training—high-intensity interval training (HIIT) and moderate-intensity continuous training (MICT)—in adults with inactive or mildly active Crohn’s disease (CD).

**Methods:**

This is a randomised, controlled, assessor-blinded, feasibility trial with three parallel groups. Forty-five adults with inactive or mildly active Crohn’s disease will be randomly assigned 1:1:1 to HIIT, MICT or usual care control. Participants in the HIIT and MICT groups will be invited to undertake three sessions of supervised exercise each week for 12 consecutive weeks. HIIT sessions will consist of ten 1-min intervals of cycling exercise at 90% of peak power output separated by 1 min of active recovery. MICT sessions will involve 30 min of continuous cycling at 35% of peak power output. Participants will be assessed before randomisation and 13 and 26 weeks after randomisation. Feasibility outcomes include rates of recruitment, retention and adherence. Interviews with participants will explore the acceptability of the exercise programmes and study procedures. Clinical/health outcomes include cardiorespiratory fitness, body mass index, resting blood pressure, markers of disease activity (faecal calprotectin and Crohn’s Disease Activity Index) and activated T cell cytokine profiles. Study questionnaires include the Inflammatory Bowel Disease Quality of Life Questionnaire, EQ-5D-5L, IBD Fatigue Scale, Hospital and Anxiety Depression Scale, and International Physical Activity Questionnaire.

**Discussion:**

This study will provide useful information on the feasibility and acceptability of supervised exercise training in adults with inactive and mildly active Crohn’s disease and will inform the design of a subsequent, adequately powered, multi-centre trial.

**Trial Registration:**

The trial is registered with the International Standard Randomised Controlled Trial Register (ISRCTN13021107). Date registration assigned was 02/12/2015.

## Background

Crohn’s disease (CD) is a relapsing inflammatory disease, affecting the gastrointestinal tract, which often presents with abdominal pain, fever, bowel obstruction or diarrhoea. In 2012, there were reported to be at least 115,000 people in the UK with CD [3]. For people in remission or with less active disease, treatment is largely directed at preventing relapse and maintaining or improving health-related quality of life [4].

Management options for CD include drug and/or biologic therapy, nutrition and diet modification, surgery and smoking cessation [4]. Physical exercise, whilst not currently part of the recommended treatment pathway, has been proposed as a potentially useful adjunctive therapy for CD by improving immunological responses and psychological health, reducing fatigue and promoting gains in muscle and bone strength [3]. However, the evidence base for exercise in CD is sparse, with only a handful of relevant studies, many of which have methodological limitations, including the use of non-randomised and non-controlled study designs and small sample sizes [3].

The effects of exercise training depend largely on the type, intensity and volume of the exercise stimulus [5]. The most common model of exercise prescription in other chronic diseases has been moderate-intensity continuous training (MICT, e.g. 30 min of moderate-intensity continuous endurance-type exercise such as swimming, cycling or jogging thrice weekly). This is well tolerated and has beneficial effects on many different aspects of physical and mental health [6]. However, a growing body of evidence indicates that shorter bouts of intense intermittent exercise—so-called ‘high-intensity interval training’ (HIIT, e.g. 1 min of hard exercise followed by 1 min of easy exercise repeated ten times)—can elicit similar physiological adaptations compared to more lengthy continuous exercise [7]. There has only been one published report investigating HIIT in people with CD to date [8], which demonstrated a single session of cycle-based HIIT was well tolerated and did not significantly increase inflammatory biomarkers in a group of 15 teenage patients. A greater understanding of the acceptability of, and chronic adaptations to, different types of exercise training is clearly warranted for safe and effective exercise promotion strategies in adults with CD.

We hypothesise that supervised exercise training will be an effective means of improving health-related quality of life, fatigue and physical and mental health in people with inactive or mildly active CD. Before embarking on an adequately powered randomised controlled trial to test this hypothesis, we have planned a feasibility study that will address several areas of uncertainty. For example, fatigue and a perceived inability to manage exercise have been cited as barriers to exercise in people with inflammatory bowel disease [9]. This raises questions about how easy it will be to recruit and retain participants in a supervised exercise training trial. The objectives of the present feasibility study are the following:To explore the acceptability, safety and potential benefits of HIIT and MICT in people with inactive and mildly active CD, relative to usual care.To evaluate the feasibility of conducting a future large-scale randomised controlled trial to assess the clinical effectiveness of exercise training in people with CD in terms of recruitment, retention, adherence and acceptability.To identify a primary outcome and estimate the parameters required to inform sample size calculation for an adequately powered randomised controlled trial.

## Methods

### Study design

EXACT (Exercise for Adults with Crohn’s disease Trial) is a multi-centre, three-arm, parallel-group, randomised controlled feasibility trial. Following baseline assessment, participants will be randomly assigned 1:1:1 to usual care plus HIIT, usual care plus MICT or usual care alone. Study assessments will be conducted at baseline and at 13 and 26 weeks after randomisation.

### Study setting

Participants will be recruited from three National Health Service (NHS) Hospital Trusts: Guy’s and St Thomas’ NHS Foundation Trust, Barts Health NHS Trust and Hampshire Hospitals NHS Foundation Trust. The exercise programmes will be delivered in the exercise science facilities of the University of East London and the University of Winchester. The study is sponsored by the University of Hertfordshire.

### Eligibility criteria

#### Inclusion criteria

Age 16–65 years.Clinical diagnosis of CD for at least 4 weeks before the screening visit.Inactive (<150 on Crohn’s Disease Activity Index [CDAI]) or mildly active (150–219 on CDAI) CD assessed no greater than 4 weeks before the screening visit.Faecal calprotectin <250 mcg/g recorded no greater than 4 weeks before the screening visit.Stable medication for at least 4 weeks before the screening visit.Willing and able to provide written informed consent and complete the study questionnaires.Willing and able to travel to the research centre for assessment visits and exercise sessions.

#### Exclusion criteria

Absolute contraindications to exercise testing and training as defined by the American College of Sports Medicine [10].Coexistent serious autoimmune disease such as rheumatoid arthritis or systemic sclerosis.Planned major surgery within the first 3 months after randomisation.PregnantFemale planning pregnancy within the first 3 months after randomisation.Poor tolerability of venepuncture.Lack of adequate venous access for required blood sampling.Current participation in >90 min/week of purposeful exercise, such as jogging or swimming.Participation in another clinical trial for with concurrent participation is deemed inappropriate.

### Interventions

#### High-intensity interval training (HIIT)

Participants allocated to the HIIT group will be invited to complete three sessions of HIIT each week for 12 consecutive weeks. It is anticipated that most sessions will be completed within normal office hours (i.e. 0900 to 1700) on Monday, Wednesday and Friday each week; however, early morning, evening and weekend sessions will be offered to facilitate attendance of participants who cannot attend on these days or times. The exercise will be performed on a calibrated, stationary upright cycle ergometer. Each session will begin with 5 min of cycling at 15% of the peak power output (*W*peak) recorded during the baseline cardiopulmonary exercise test. The main body of each session will involve ten 1-min bouts of cycling at 90% of *W*peak, interspersed with 1-min bouts of cycling at 15% of *W*peak [11]. The session will end with 3 min of cycling at 15% of *W*peak. Similar protocols of HIIT have been shown to be safe and effective for improving cardiorespiratory fitness in various clinical and non-clinical populations [12, 13]. Incremental cycle exercise testing, without the analysis of expired gases and blood lactate responses, will be performed during the final sessions of the fourth and eighth week of training (i.e. at sessions 12 and 24 of 36) and will replace the normal exercise training of those sessions. The peak power output recorded during these tests will be used to adjust the power output used within the training sessions (i.e. the training will be progressed after 4 and 8 weeks according to changes in peak power output assessed using incremental cycle exercise testing).

Each session will be supervised by a research assistant who will have received specific training from the investigators in how to deliver the exercise protocol. A maximum of four participants will be trained per session. A specifically designed exercise session case report form (CRF) will be completed for each exercise session. Prior to exercise, and 10-min post-exercise, the participant’s resting heart rate and blood pressure will be recorded (Omron, M2, The Netherlands). Differential ratings for breathlessness and leg exertion will be assessed using Borg’s CR-10 scale [14] before exercise, immediately post, and 10-min post-exercise. In addition, participants will be asked to rate their breathlessness and leg exertion at 2.5, 7.5, 42.5, 47.5, 92.5 and 97.5% of exercise completed. These time points were chosen to incorporate both interval and recovery periods during the HIIT protocol [15]. Participants’ heart rate will also be recorded using Polar heart rate monitors at 2.5, 42.5 and 92.5% of exercise completed. The one item Feeling Scale (FS; [16]) will be used to measure general affective valence (i.e. pleasure and displeasure). Participants will be prompted at the beginning of each exercise visit with the following instructions: ‘While participating in exercise, it is common to experience changes in mood. Some individuals find exercise pleasurable, whereas others find it to be unpleasant. Additionally, feeling may fluctuate across time. That is, one might feel good and bad a number of times during exercise. When asked, please tell me how you feel at that current moment using the scale below.’ The feeling scale is scored on an 11-point bipolar scale ranging from −5 (very bad) to +5 (very good). The FS will be administered pre-, immediately post and 10-minutes post-exercise. To assess in-task affect, the FS will be administered at 2.5, 42.5 and 92.5% of exercise completed. The collection of such data will permit a detailed quantification of the exercise intervention. The research assistant will be required to email a copy of the anonymised exercise session CRF for sessions 1, 13 and 25 to a member of the trial management team so that they can confirm that the CRF and sessions are being completed appropriately.

Overall enjoyment of the exercise programme will be assessed during the week 13 assessment, using the validated multi-dimensional Physical Activity Enjoyment Scale (PACES) [17]. This will typically be 3–7 days following completion of the overall programme, allowing participants’ reflection and evaluation time. Participants in the control group will not be required to complete this.

#### Moderate-intensity continuous training (MICT)

Participants allocated to the MICT group will be invited to complete three cycle-based exercise sessions each week for 12 weeks, with each session involving a warm-up and cool-down of cycling at 15% of *W*peak. The main body of each exercise session in this group involves 30 min cycling at 35% of *W*peak. This programme has been selected because it has been shown to elicit a similar energy expenditure compared with the HIIT programme [11]. As described for the HIIT group above, the training will be progressed according to changes in peak power output re-assessed after 4 and 8 weeks. Heart rate, perceived exertion and general affective valence will be recorded at the same relative time points as in the HIIT group.

Both exercise programmes will be delivered in addition to usual care. Participants in both exercise groups will be able to claim up to £10.90 per session for travel expenses.

After completing the 12-week intervention period, all exercise group participants will receive an individualised exercise programme that they can manage on their own. The exercise prescription will largely reflect the content of the supervised exercise programme; however, for example, the mode of exercise may change if a cycle ergometer cannot be easily accessed by the participant.

#### Usual care control group

This group will not receive any supervised exercise or be given any specific recommendations regarding exercise. However, once control participants have completed the 26-week assessment, they will be offered a one-to-one exercise consultation via telephone with the research assistant in which they will discuss the benefits of exercise training, barriers and facilitators of exercise, exercise guidelines and personal goals and action plans. The aim of offering this consultation to control participants is to help minimise the potential for resentful demoralisation that may occur through being allocated to this group [18].

### Outcome measures

#### Feasibility and acceptability outcomes

The main focus of this study is feasibility and acceptability of procedures for recruitment, allocation, measurement, retention and the intervention procedures. Recruitment rates will be measured as rate of invited participants who are eligible and consenting and will be reported in a Consolidated Standards of Reporting Trials (CONSORT) participant flowchart. Acceptability of allocation procedures will be assessed by examining reasons for dropout in discontinuing participants and comparing attrition rates between the three study groups and between participants who did and did not receive their preferred allocation (assessed prior to randomisation). Suitability of measurement procedures will be evaluated based on completion rates and rates of missing data. Attrition rates will be established as discontinuation of intervention and loss to follow-up measurement for all groups. The acceptability of the exercise programmes will be assessed using session adherence rates, measures of exercise enjoyment (see the Interventions section) and participant and provider feedback via telephone interviews conducted after the 26-week follow-up visit. The participant interviews will last up to 30 min and will cover perceived benefits and negative consequences from participating in the study, feedback regarding specific design features of the study (including the exercise protocol and assessment procedures) and perceptions of barriers and facilitators to intervention participation. The safety of exercise training will also be assessed by exploring rates of disease relapse at 13 weeks, reasons for dropout from the exercise programmes and the number and type of adverse events, both CD specific and general, which occur in each group.

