### Sample size

As this is a feasibility study, no formal sample size calculation was performed [26]. Instead, this study follows sample size recommendations for pilot randomised controlled trials [27] and aims to have at least 12 participants per study arm who provide full data. We aim to recruit 15 participants to each group (i.e. total sample size of 45) to allow up to 20% attrition, which is appropriate based on our exercise studies in other clinical populations [28–30]. This number of participants is deemed adequate to provide sufficient information on key feasibility issues such as recruitment, retention and acceptability of the exercise programmes.

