### Ethical and safety considerations

The research study will follow the Health Research Authority’s processes for gaining NHS permissions and approvals. We are confident that the assessment procedures and exercise programmes will be safe. Exercise testing has been demonstrated to be safe for patients with CD [30] and other chronic diseases [31, 32]. Nevertheless, patients’ suitability for the study will be assessed by a clinical co-investigator, and participants will be closely monitored during all training and testing sessions. Furthermore, exercise sessions will be supervised by experienced staff who are trained in resuscitation. Exercise training will be discontinued if a clinical co-investigator deems it necessary (e.g. if a patient experiences a disease relapse) or if the participant withdraws consent. The trial will also be subject to oversight from an independent Trial Steering Committee.

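### Attrition is compared by received preference without regard to arm, so unequal attrition between arms can pass for a preference effect; the attrition definition should also separate stopping exercise from loss to follow-up.

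*Protocol article*

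**What the plan says.** The Protocol article, under Feasibility and acceptability outcomes, sets out how acceptability of allocation is to be judged: "Acceptability of allocation procedures will be assessed by examining reasons for dropout in discontinuing participants", together with "comparing attrition rates between the three study groups and between participants who did and did not receive their preferred allocation". Preference is recorded before randomisation. The same paragraph defines attrition: "Attrition rates will be established as discontinuation of intervention and loss to follow-up measurement for all groups".

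Three other places bear on this:

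- Usual care control group: "This group will not receive any supervised exercise or be given any specific recommendations regarding exercise". The telephone exercise consultation offered to controls comes only after the 26-week assessment. The section gives the reason for offering it: the protocol foresees that controls may be demoralised by their allocation.
- Ethical and safety considerations: "Exercise training will be discontinued if a clinical co-investigator deems it necessary". A participant can therefore stop the intervention without necessarily leaving the study.
- Sample size: 15 participants per arm are sought "to allow up to 20% attrition", so that at least 12 per arm give full data.

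The text does not say that the preference comparison is made within arm or adjusted for arm. It does not say whether discontinuation and loss to follow-up form one rate or two.

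**The concern.** Randomisation makes a person's preference independent of the arm received. It does not make receiving one's preference independent of arm. If few people prefer usual care, few controls can be in the group that got what it wanted, and controls make up a large part of the group that did not. Any difference in attrition between usual care and exercise, whatever its cause, then appears as a difference between preference groups.

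The definition raises a second, smaller question. If its two components are combined into one rate, that rate contains an event that only exercise participants can have. Someone who stops cycling but attends week 13 would count, and a control in the same health who attends would not.

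At stake is what the study says about acceptability of allocation and about retention. The protocol calls feasibility and acceptability its main focus, and these comparisons are its stated quantitative test of allocation. A misread preference effect could affect how allocation is handled in the main trial.

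**Working it through.** **The plan's own figure.** 12 / (1 - 0.20) = 15 per arm, and 3 x 15 = 45. This reproduces and is not in dispute.

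**Composition of the preference groups.** The allocation ratio of 1:1:1 is from Randomisation and allocation concealment. Let q_a be the share preferring arm a, among participants who state a preference.

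- Chance of receiving the preferred arm: 1/3, whatever the preference.
- Share of arm a among the matched (preference received): (q_a/3) / (1/3) = q_a.
- Share of arm a among the unmatched: ((1 - q_a)/3) / (2/3) = (1 - q_a)/2.

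With attrition r_a in arm a and no effect of preference, the expected matched-minus-unmatched difference is the sum over arms of r_a(3q_a - 1)/2. If both exercise arms have rate r_E and usual care has r_C, with share q_C preferring usual care, this becomes (r_C - r_E)(3q_C - 1)/2. It is zero when r_C = r_E or when q_C = 1/3.

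**Example on loss to follow-up alone.** The documents give no preference distribution and no attrition by arm, so these rates are assumptions: r_E = 15%, r_C = 30%.

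| Share preferring usual care | Matched | Unmatched | Difference (points) |
|---|---|---|---|
| 0 | 15.0% | 0.5 x 15 + 0.5 x 30 = 22.5% | -7.5 |
| 10% | 16.5% | 21.75% | -5.25 |
| 20% | 18.0% | 21.0% | -3.0 |
| 1/3 | 20.0% | 20.0% | 0 |
| 50% | 22.5% | 18.75% | +3.75 |

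Every row has no preference effect. Within each arm the matched and unmatched rates are equal, so a within-arm comparison would correctly show zero.

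**If attrition is read as one combined rate.** Assume loss L in every arm and independent discontinuation D in the exercise arms.

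- Exercise: 1 - (1 - L)(1 - D). Usual care: L. Gap: (1 - L)D.
- L = 20%, D = 20%: 1 - 0.8 x 0.8 = 36% against 20%, a gap of 16 points with identical loss to follow-up.
- Over L of 10 to 20% and D of 10 to 30%, the gap runs from 0.8 x 0.1 = 8 points to 0.9 x 0.3 = 27 points.
- Preference comparison at 36% and 20% with nobody preferring usual care: matched 36%, unmatched 0.5 x 36 + 0.5 x 20 = 28%, a difference of +8 points. Over the same L and D, with 0 to 50% preferring usual care, the difference runs from -6.8 to +13.5 points.

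**Precision.** About 45/3 = 15 participants would be matched and 30 unmatched. For 36% against 28%, the 95% half-width is 1.96 x sqrt(0.36 x 0.64/15 + 0.28 x 0.72/30) = 0.29, or 29 points.

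**The case against.** Much can be said for the protocol. The definition speaks of rates in the plural and can be read as two separate rates; the three-group comparison of loss to follow-up is then sound. A detailed analysis plan is announced under Statistical analysis and is not shown; it may separate the components or stratify by arm. Feasibility outcomes are descriptive, and no hypothesis testing is planned. Reasons for dropout are to be examined, which would help to tell stopping exercise from leaving the study. The preference bias needs both uneven preferences and unequal attrition, and the documents establish neither. All of this stands, and it limits the point. It does not remove it, because the preference comparison is stated in the protocol, and as stated it ignores arm.

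Three stronger conclusions that a reader might infer are not supported:

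- *Both comparisons are confounded with arm.* In the three-group comparison arm is the randomised exposure and cannot confound it. The most that can be said is that, on the single-rate reading, the outcome is not comparable across arms.
- *Attrition is higher in the exercise arms by definition.* Even a combined rate is higher only if some participants stop exercise yet attend, and if loss among controls does not offset this. The protocol's own worry about demoralised controls points the other way.
- *The 20% allowance cannot be checked.* It is tied to participants with full data. Missing-data rates, the CONSORT flow diagram and the count of valid 13-week data in Criteria for success all allow a check.

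**Conclusion.** The point holds in a limited form. Followed as written, the comparison by received preference can show a difference where preference has no effect. Its size and sign depend on unknowns: under the assumed 15% and 30% loss it runs from -7.5 points if nobody prefers usual care, through zero at one third, to +3.75 points if half do. Uneven preference is plausible among volunteers for an exercise trial, but that is a judgement and not a figure from the documents. Separating the two components of attrition does not cure this, since the example uses loss to follow-up alone.

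The definition is ambiguous rather than wrong. Only if it means a single rate is the three-group comparison not like-for-like, by 8 to 27 points under the assumptions shown.

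The practical weight is moderate. The success criteria rest on interviews, adverse events, session adherence, recruitment and valid 13-week data, so no decision to proceed turns on either comparison. The numbers are too small for either to be precise.

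**What to change.** 1. State two rates: loss to follow-up measurement at 13 and 26 weeks for all three arms, which is the rate compared between arms, and discontinuation of intervention for HIIT and MICT only.
2. Present loss to follow-up by received preference within each arm, or combine the within-arm differences across arms with stratification by arm. Show participants with no preference separately.
3. Note that an arm nobody prefers has no matched participants and so gives no contrast.

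The cost is a change of wording and one extra table; no new data are needed. The drawback is small cells. If nobody prefers usual care and the rest split evenly, each exercise arm of 15 divides into about 7 and 8, where one dropout moves a rate by 1/8 = 12.5 to 1/7 = 14.3 points. The table should therefore be presented as descriptive, with counts, and read beside the reasons for dropout.

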### Criteria for success

This feasibility trial will be deemed successful and lead to the development of a proposal for an adequately powered randomised controlled trial if:1. At least one of the exercise programmes is shown to be acceptable, based on a combination of data from participant interviews, the number and type of adverse events in each group and exercise session adherence rates (at least 67% of participants completing at least 24 of the 36 sessions).2. At least 24 patients are recruited during the 12-month recruitment window (based on recruitment from three NHS Hospital Trusts and 1–2 recruits per site per two months).3. At least 67% of participants provide valid cardiorespiratory fitness, disease activity (CDAI) and quality of life (IBDQ) data at the 13-week follow-up visit.

The criteria for success will provide the basis for interpreting the results of this study and determine whether it is appropriate to proceed to a full trial and if any modifications need to occur for a full trial to be feasible.

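### Acceptability interviews are set only after week 26, so participants who withdraw or are lost are the least likely to be heard in success criterion 1

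*Protocol article*

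**What the plan says.** In the protocol article, Feasibility and acceptability outcomes, programme acceptability rests on session adherence, enjoyment measures and "participant and provider feedback via telephone interviews conducted after the 26-week follow-up visit". The participant calls last up to 30 minutes. They cover benefits and drawbacks of taking part, views on the exercise protocol and assessments, and what helped or hindered participation. No interview at discontinuation, at withdrawal or at the end of training is described.

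Under Criteria for success, criterion 1 judges whether at least one programme is acceptable, "based on a combination of data from participant interviews, the number and type of adverse events in each group and exercise session adherence rates". Only the adherence component has a number: "at least 67% of participants completing at least 24 of the 36 sessions".

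The supervised programme is "three sessions of HIIT each week for 12 consecutive weeks", and the moderate-intensity arm also trains for 12 weeks. The Sample size section "aims to have at least 12 participants per study arm who provide full data" and sets recruitment at 15 per arm "to allow up to 20% attrition".

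**The concern.** Tying the call to the week-26 visit favours people still in follow-up. Those who withdrew or were lost have no such visit, yet on the obstacles and drawbacks that the interview covers they are likely to have the most to say. The Background names fatigue and doubt about coping with exercise as reasons why recruitment and retention are uncertain, so these are people the trial needs to understand.

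Someone who stops training but stays in follow-up can be interviewed, but only long after the event. For completers too, the self-managed exercise programme described under Interventions falls between the training and the call.

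At stake is the interview component of a go/no-go criterion. The same section says the criteria also show whether a full trial needs modifications, and missing the accounts of those who left weakens that use as well.

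**Working it through.** **Plan's own figure.** Inputs from Sample size: 12 per arm with full data, attrition up to 20%. 12 / (1 − 0.20) = 15 per arm, and 3 × 15 = 45. The stated target is reproduced and is not in dispute.

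**People at issue.** The two exercise arms hold 2 × 15 = 30 participants. At the planned attrition, 0.20 × 15 = 3 per arm, or 0.20 × 30 = 6 of 30. This is an upper figure on the plan's own allowance, for two reasons:
- the allowance concerns people without full data, not only those who leave;
- the outcomes section counts both stopping the intervention and loss to follow-up as attrition, and people in the first group may still reach week 26.

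**Delay.** Training ends at about week 12 and the earliest interview follows week 26: 26 − 12 = 14 weeks. The gap is longer for anyone who stops sooner. As an illustration, stopping at week 4 (an assumed value) gives 26 − 4 = 22 weeks.

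**What the adherence component already catches.** 0.67 × 15 = 10.05, so 11 of 15 in an arm must complete 24 sessions. Ten of 15 is 66.7% and fails. Up to 4 of 15 may fall short and the arm still meets this component. If adherence is counted over everyone allocated, people who stop early count against the programme, but the figure does not say why they stopped.

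**Other sources, set against criterion 1.**

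| Source | Covers people who left? | Named in criterion 1? |
|---|---|---|
| Session adherence | Yes, if counted over all allocated; gives no reasons | Yes |
| Adverse events, including those leading to withdrawal from a programme (Safety reporting) | Yes, where an event caused it | Yes |
| Reasons for dropout | Yes | No; placed under allocation procedures and safety |
| Provider interviews | Second-hand | No; only participant interviews are named |
| Enjoyment scale at week 13 | Only those who attend | No |
| Feeling Scale at each session | Until they stop attending | No |

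No row supplies the withdrawn participant's own full account of barriers and drawbacks.

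**Size of the tilt.** The protocol plans no proportion favourable from the interviews and gives no views of those who leave. Neither quantity needed for a bias calculation is available.

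**The case against.** The strongest reply is that a time is not an eligibility rule. A telephone call after week 26 does not require attendance at the visit, nothing excludes people who stopped, and the full protocol may say how they are approached. This stands in part: the text does not bar them. But the article does fix the timing, and the point concerns that stated choice, not missing detail.

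Second, stopping exercise is not leaving the trial. This stands and narrows the point. Selection applies mainly to those who withdraw or are lost; for those who stop but remain, the issue is delay.

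Third, the table's other sources already register dropout. They limit the effect but do not replace the interview.

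Fourth, the timing has merit. It lets participants comment on every assessment and on the self-managed phase, and it keeps the interview from influencing the 26-week questionnaires. That is a good reason to retain it for those in follow-up. It has no force for people who will complete no further questionnaires.

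A reader might also infer a larger problem from criterion 3, which requires that "At least 67% of participants provide valid cardiorespiratory fitness, disease activity (CDAI) and quality of life (IBDQ) data at the 13-week follow-up visit", and take the remaining third as people who will never be interviewed. The document does not support that. Criterion 3 concerns valid data among all participants, not exercisers alone, and someone who attends but whose exercise test fails the validity rules also falls short.

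**Conclusion.** The concern holds in a limited form. With interviews set only after week 26, participants who withdraw or are lost are the least likely to be heard, and early stoppers who remain are heard late. The likely direction is towards judging a programme acceptable. This assumes that the timing is followed as written and that those who leave hold, on average, less favourable views. The second assumption is plausible but is not stated in the protocol.

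The only size the document supports is a head count: up to 6 of 30 exercise participants at the planned attrition. A reader might want to turn this into an inflated percentage of acceptability, but the interviews are qualitative and no such percentage is planned. Nor does the timing decide criterion 1 alone, since adherence and adverse events enter the same judgement. The change is worth making because it is cheap, and the Trial status section reports recruitment as ongoing. No figure in the protocol is wrong on this point.

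**What to change.** - Keep the post-week-26 interview for participants still in follow-up.
- Offer the same telephone interview, at the time of stopping, to anyone who discontinues the exercise programme or withdraws from the study.
- Report the numbers interviewed and the themes by arm and completion status. Giving the numbers approached as well would show who declined or could not be reached.
- State that criterion 1 weighs the accounts of both completers and those who stopped.

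The cost is a minor amendment and a few calls of up to 30 minutes made earlier than planned. The downside is that people who stop training but stay in follow-up will complete later questionnaires having already been interviewed. Some who leave will decline or be out of reach, so the gap will narrow but not close.
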